#### Selection and recruitment

2.2.2

Patients will be screened for inclusion criteria using hospital’s indoor database, the ICD-10 codes and the schedule of elective screening and diagnostic colonoscopies, endoscopic polypectomies, and surgery for CRC (laparoscopic colon resections, in particular). Preliminary selected patients will be contacted, double-checked for inclusion, and asked for participation (by phone or tête-à-tête). Agreed patients will be provided with health questionnaires and stool collection kits in person or by mail. The overall study design is depicted in **Figure 1**.

#### Questionnaires and physical evaluation

2.2.3

The personal information of the subjects will be conducted through the hospital’s indoor database and advanced health information questionnaires. Patients will be provided with questionnaires containing questions on demographics, anthropometric data (height, weight, body mass index (BMI) and waist circumference), health history, gastrointestinal disorders and interventional procedures, bowel symptoms, co-morbidities (including tobacco and alcohol consumption), use of certain medication (as antibiotics, probiotics, statins, proton pump inhibitors, corticoids and immunomodulators), dietary and ecological habits and possible microplastic intake. Physical evaluation will be assessed by the anesthesiologist on the procedure day.

#### Sample size calculation

2.2.4

Since there is no clinical trial assessing the composition of intestinal microbiota; the count, density and distribution of immunocompetent cells in epithelial and stromal compartments, and the interrelations of both along every step of conventional adenoma-carcinoma pathway and healthy colon, endpoints of the study are currently unable to be determined. Thus, the sample size is estimated based on the data from a previous clinical trial (36), where 10 participants per group had 80% power at an alpha level of 0.05 and beta level of 0.2 to detect significant differences. The sample size in this study was calculated statistically by G*Power 3.1.9.4. Considering the expected withdrawal of participants during the intervention, we plan to recruit from 10 to 15 participants per group. This results in minimum 50 patients, 190 biopsy locations, 570 tissue samples, and a total number of 2280 specimens (staining using 4 antibodies) to be examined histologically and immunohistochemically. Plus 50 fecal and 570 tissue samples to be 16S rRNA sequenced (after DNA extraction) for precise analysis of gut microbiota structure. Overall, despite the inter-individual heterogeneity, with this sample size, differences in gut microbiota composition and local immunity changes are considered to be detectable.

## Interventions

3

Adult patients who have been referred to a screening/diagnostic/therapeutic colonoscopy and during procedure will be diagnosed with CR polyps, as a common practice of colorectal dysplasia management will undergo (if no contraindications):

- endoscopic polypectomy, in case of simple CR adenoma;- endoscopic mucosal resection (EMR) or endoscopic submucosal dissection (ESD), in case of advanced, flat/over the fold/right-sided colon CR adenomas or Ca in situ;- TEM (transanal endoscopic microsurgery) in case of large rectal adenomas or Ca in situ;- sampling and subsequent colon resection in case of colorectal cancer or unresectable colon polyps.

During the same procedure seven mucosal biopsy specimens from each region (macroscopically healthy right- and left-sided colon, terminal ileum, and pathologic lesion, if present) will be obtained. In order to prevent possible cross-contamination from other parts of the bowel (especially important in tissue specimens being sampled for microbiota compositional analysis), sterile biopsy forceps will be used for each region and each biopsy location. Resected polyps and mucosal biopsy specimens from unaffected bowel regions will be sent to histological, IHC, DNA sequencing examination and further genetic testing for specific oncogenic mutations (in the next trial). In terms of the study, no further visits to the hospital will be required.

### Data collection and management

3.1

Assessment of participants will be conducted at the pre-procedure (-t1), procedure (0) and post-procedure (t1-t4) timepoints. The detailed schedule of assessments is depicted in **Table 1**. The primary outcomes will be the differences in the microbiota composition and immune infiltration in different localizations of the tumor and different steps of mucosa dysplastic lesions compared to healthy controls. The secondary outcomes include correlation analysis of gut microbial diversity, intestinal immunity variables and the grade of colorectal dysplasia assessed for the study.

**Table 1 T1:** Study schedule of enrolment, interventions, and assessments.

	STUDY PERIOD						
	Enrolment	Allocation	Examination and analysis period				Close-out
TIMEPOINT	*-t_1_ *	0	*t_1_ *	*t_2_ *	*t_3_ *	*t_4_ *	*t_x_ *
ENROLMENT:							
Eligibility screen	X						
Informed consent + filling the questionnaire	X						
Allocation		X					
INTERVENTIONS:							
Collection of fecal samples	X	X					
Colonoscopy + endoscopic polypectomy (or biopsy) and normal gut tissue sampling or right hemicolectomy and gut tissue sampling	X		X				
ASSESSMENTS AND DATA ANALYSIS:							
Pathologic investigations: HE and IHC	X	X	X				
16S rRNA gut tissue- and fecal-derived microbiota sequencing			X	X	X	X	
AI-based digital image analysis			X	X	X	X	
Qualitative data analysis based on the questionnaires		X	X				
Data analysis on intestinal immune infiltration variables: count, density, and distribution of CD3, CD8, CD20, CD68 cells in epithelial and stromal compartments				X	X	X	X
Data analysis on gut microbiota compositional changes in tissue and stool samples: relative abundance, α- and β-diversity, etc.				X	X	X	X
Correlation analysis of gut microbiota and immune response variables in different site of the colon along the adenoma-carcinoma sequence						X	X

X, mark the appropriate period for the enrollment, interventions and other activities during the project

#### Pre-procedure

3.1.1

The collection of feces will be carried out prior to bowel preparation for colonoscopy or surgery (from 2 weeks until the planned procedure) at the residence. That way extensive alterations due to bowel cleansing in (only partially constant) individual intestinal luminal microbiota could be avoided. Briefly, participants will be instructed to, firstly, pass stool on the tray, secondly, dig up 1-3 spoons of stool and, thirdly, insert it into a sterile screw cap container. For reducing the change of microbiota composition in the stools, the liquid preservative will be added in each container sent to the preliminary participants. Patients will be asked to bring stool samples to the researcher at the hospital on the procedure day. Those with completed questionnaires, collected stool samples and written informed consent will eventually be enrolled in further study.

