**Methods and analyses:**

This study aims to prospectively recruit 40 patients (10 per group) with confirmed colorectal dysplasia undergoing endoscopic polypectomy, endoscopic mucosal resection for colorectal small (≤1cm), and large (>1cm) adenoma or carcinoma in situ, or biopsy and subsequent colon resection for invasive colorectal cancer, and 10 healthy patients undergoing screening colonoscopy. Stool samples will be collected prior to bowel preparation for the analysis of fecal (luminal) microbiota composition. Biopsy specimens will be taken from the terminal ileum, right colon, left colon, and a pathological lesion in the colon (if present) to assess mucosa-associated microbiota composition and intestinal immunity response. DNA will be extracted from all samples and sequenced using the Illumina MiSeq platform. Unifrac and Bray-Curtis methods will be used to assess microbial diversity. The intestinal immune system response will be examined using digital image analysis where primarily immunohistochemistry procedures for CD3, CD8, CD20 and CD68 immune cell markers will be performed. Thereafter, the count, density and distribution of immunocompetent cells in epithelial and stromal tissue compartments will be evaluated using AI-based platform. The interaction between the microbial shifts and intestinal immune system response in adenoma-carcinoma sequence and the healthy patients will be examined. In addition, fecal samples will be explored for gut microbiota’s composition, comparing fecal- and tissue-derived bacterial patterns in healthy gut and along the adenoma-carcinoma sequence.

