### Study population

2.2

Adult patients (from 18 years old) who will be referred for a colonoscopy either through the bowel cancer screening program, or as a part of a surveillance program, or due to symptoms and diagnosed with histologically confirmed colorectal dysplasia (exposure groups) or adult patients without any polypoid lesions found during the colonoscopy (control group). It is expected that most of the participants will be referred due to iron deficiency anemia, altered bowel habits, weight loss, rectal bleeding, planned polypectomy, CRC-associated family history, abnormal imaging, or polyp surveillance.

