#### Procedure

3.1.2

Highly experienced endoscopists, with proven adenoma detection rate of >30% will perform the colonoscopy, endoscopic polypectomy (if needed) and tissue sampling intended for the study. In case of CRC or endoscopically unresectable polyps, experienced abdominal surgeons specializing in colorectal surgery will take over the sampling procedure, as well. Patients will undergo simple polypectomy, endoscopic mucosal resection (EMR), endoscopic submucosal dissection (ESD), transanal endoscopic microsurgery (TEM) or surgery for CRC depending on the localization, size and histology of the lesion found. Procedures are scheduled as a common management of a colorectal neoplasm and will not be affected by patient’s preliminary enrolment in the study. During colonoscopy or colon resection the mucosal biopsy specimens from the polypoid lesion and the healthy gut (macroscopically healthy right- and left-sided colon and terminal ileum) will be obtained using disposable biopsy forceps (separate for each segment) to avoid bacterial contamination. The tissue sampling plan includes a) tissue of the terminal ileum; b) tissue of the right-sided colon (cecum, ascending colon, right colic flexure); c) tissue of the left-sided colon (descending colon, sigmoid colon and the rectosigmoid junction); and d) tissue of the lesion (if present). In case of small adenomas (<1 cm size), sampling is performed near the lesion, since multiple biopsies directly from the small tumor may result in artificial material fragmentation, at the same time raising the risk of histological misdiagnosis. Hyperplastic polyps and non-polypoid lesions are not being sampled, nor resected during colonoscopy in terms of the study. If multiple diverticula are present, normal tissue of the colon will be sampled at the least affected site. More than ten locoregional polyps are considered as polyposis and are not further investigated under this trial. Otherwise, while up to ten polyps are detected in the same colon region, the largest is being picked for sampling and subsequent investigation. Inflammatory or pseudo-polyps are not adenomatous lesions, thus are not considered eligible for the study. Bowel preparation should be evaluated with at least 6 out of 9 points according to the Boston Bowel Preparation Scale (BBPS), otherwise precise detection and evaluation of dysplastic mucosal lesions cannot be ensured. Those patients who underwent colonoscopy and have been evaluated by less than 6 points according to BBPS will not be included in further study. Resected or sampled polyps should be described using the Paris and NICE classifications. Each stool and tissue sample will be encoded according to localization of the colon and the type of examination it is dedicated for.

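### Stool is protected only from cleansing for the planned procedure; an earlier diagnostic bowel preparation, likely more common in lesion groups than in controls, is neither dated nor used in the analysis (minor)

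*Protocol article*

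**What the plan says.** **Timing rule.** Section 3.1.1 (Pre-procedure) states that the "collection of feces will be carried out prior to bowel preparation for colonoscopy or surgery (from 2 weeks until the planned procedure"). The reason given there is to avoid changes that cleansing causes in the luminal microbiota, which the section calls extensive.

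**Who is recruited, and when kits are given.** Section 2.2.2 (Selection and recruitment) draws patients from "the schedule of elective screening and diagnostic colonoscopies, endoscopic polypectomies, and surgery for CRC (laparoscopic colon resections, in particular"). It then says: "Agreed patients will be provided with health questionnaires and stool collection kits in person or by mail". The kit therefore follows selection and agreement.

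**Where study tissue is taken.** Section 3.1.2 (Procedure) says: "During colonoscopy or colon resection the mucosal biopsy specimens from the polypoid lesion and the healthy gut". Table 1 in section 3.1 likewise lists right hemicolectomy with tissue sampling as an alternative to colonoscopy with sampling.

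**Care pathway in cancer.** Section 3 (Interventions) gives "sampling and subsequent colon resection in case of colorectal cancer or unresectable colon polyps", and the abstract has "biopsy and subsequent colon resection for invasive colorectal cancer". Section 3 also describes a one-procedure route: "During the same procedure seven mucosal biopsy specimens from each region".

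**Controls.** Section 2.2.1.2 takes them from screening colonoscopy with no polypoid lesion found.

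**Look-back periods.** Section 2.2.1.3 sets them for antibiotics, pre- and probiotics, statins, proton pump inhibitors, steroids, gut infection and chemo- or radiotherapy. It has none for an earlier bowel preparation. Section 2.2.3 asks about past interventional procedures but attaches no rule to the answer.

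**The concern.** The rule guards against cleansing for the procedure at which the study samples are taken. It does not reach back to an earlier one. A patient already listed for cancer resection will usually have been diagnosed at a prepared colonoscopy before any stool kit was handed over. The same can hold for a patient listed for a planned polypectomy. A control at a screening colonoscopy need not have had any preparation before.

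If an earlier cleansing still affects the stool when it is collected, the exposure would be unevenly spread across groups, probably heavier in the later stages. The difference between cancer and control stools would then mix disease with recent preparation. This touches the secondary objective in section 1.2 that compares fecal and mucosal microbiota in healthy patients and along the adenoma-carcinoma sequence. It also bears on the suggestion in section 5.1 that bacterial patterns might supplement stool-based detection of adenoma. Without the date of the last preparation, nobody could show afterwards whether this mattered.

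**Working it through.** **Step 1: which routes are covered.** The protocol gives no figure on this point, so the sections are set side by side.

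- *Entry at a colonoscopy list, sampled at that colonoscopy* (section 3; Table 2 defines Group IV as endoscopically sampled). Stool precedes the only study-related preparation, and the rule works.
- *Entry at the surgery list, sampled at resection* (sections 2.2.2, 3.1.1, 3.1.2 and Table 1). Stool precedes the surgical preparation. A diagnostic colonoscopy will usually have come before that, and no interval since it is set.
- *Entry at a planned polypectomy list* (sections 2.2 and 2.2.2). An earlier prepared colonoscopy is possible, and again no interval is set.
- *Controls at screening colonoscopy* (section 2.2.1.2). An earlier preparation is neither required nor barred.

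So exposure to an earlier preparation can differ by group, and nothing in the document measures it for the analysis.

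**Step 2: what an imbalance could do (illustration).** The documents give no share of patients entering at surgery, no time from diagnosis to surgery, and no duration of a cleansing effect. All exposure shares and shifts below are therefore assumptions. Only the 10 patients per group and the 0.05 level come from the protocol (sections 2.2.4 and 4).

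False group shift = (share exposed in Group IV − share exposed in controls) × residual shift d. With 2 of 10 controls exposed:

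| Group IV exposed | d = 0.2 SD | d = 0.5 SD | d = 1.0 SD |
|---|---|---|---|
| 5 of 10 | 0.3 × 0.2 = 0.06 | 0.3 × 0.5 = 0.15 | 0.3 × 1.0 = 0.30 |
| 8 of 10 | 0.6 × 0.2 = 0.12 | 0.6 × 0.5 = 0.30 | 0.6 × 1.0 = 0.60 |
| 10 of 10 | 0.8 × 0.2 = 0.16 | 0.8 × 0.5 = 0.40 | 0.8 × 1.0 = 0.80 |

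Simulated rejection rate of an exact two-sided Mann-Whitney test at 0.05, 10 against 10, normal data with no true difference:

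| Exposed, IV vs controls | d = 0.2 SD | d = 0.5 SD | d = 1.0 SD |
|---|---|---|---|
| 5 vs 2 | about 4% | about 5% | about 6% |
| 8 vs 2 | about 5% | about 8% | about 18% |
| 10 vs 2 | about 5% | about 11% | about 32% |
| 5 vs 5 | about 4% | about 4% | about 2% |

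With no exposure the rate is about 4%, the exact test being slightly conservative at this size. Balanced exposure does not inflate the error. Inflation needs both a clear imbalance and a residual shift of roughly 0.5 SD or more.

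**Step 3: what a restricted comparison would cost.** The difference detectable with 80% power by a two-sided t-test at 0.05 is 1.32 SD with 10 against 10. With 7 Group IV stools left against 10 controls it is 1.48 SD, and with 5 left it is 1.66 SD. These indicate scale only. For community composition and taxa, section 4 names ANOSIM, ANCOM and LEfSe, not a t-test.

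**The case against.** Nothing in section 3.1.1 is wrong as written, and on the one-procedure route it does its job. Section 3 adds that no further hospital visits are needed, and Table 2 describes Group IV as endoscopically sampled. Both fit colonoscopy as a common study procedure, with stool collected first. The wording about biopsy or sampling and later resection describes the care pathway; taken alone it does not show that study stool follows the diagnostic colonoscopy. The article is also condensed. The questionnaire itself is not shown, so it may already ask for dates, and the redundancy analysis in section 4 could take such a variable. Finally, the harm requires an effect that lasts until collection, and the documents are silent on duration. At an assumed residual of 0.2 SD the error rate hardly moves.

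Most of this stands, and it limits the weight of the point. It does not remove it: entry at resection is provided for in sections 2.2.2, 3.1.1, 3.1.2 and Table 1, and no section sets or uses an interval since an earlier cleansing.

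A reader might go further in three ways, none of which the documents support:

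- *That cancer-group stools as a whole are compromised.* The share entering at surgery is not given, and patients sampled at their diagnostic colonoscopy are protected.
- *That controls are free of earlier preparation.* Section 2.2 speaks of patients "referred for a colonoscopy either through the bowel cancer screening program, or as a part of a surveillance program, or due to symptoms", and no criterion bars an earlier colonoscopy in controls.
- *That tissue comparisons are safe, or equally affected.* The document does not say either way.

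**Conclusion.** The point holds as a minor one. The stool rule covers only the preparation for the planned procedure. Patients from the cancer surgery or planned polypectomy lists will often have had an earlier prepared colonoscopy, whereas screening controls need not have. A residual cleansing effect could therefore be confounded with stage in the between-group stool comparisons.

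The size is unknown and may be nil: nil if the microbiota has recovered by collection, or if exposure is balanced between groups. The larger rates in the illustration rest on assumed near-complete exposure in Group IV and an assumed residual shift of 1.0 SD; they are not estimates for this study. That an earlier colonoscopy is frequent among surgical entrants is an inference from the care pathway, not a statement in the protocol.

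**What to change.** 1. Add to the section 2.2.3 questionnaire the date of the last bowel preparation before stool collection, for every participant including controls.
2. Report the interval from that preparation to stool collection by group.
3. State an interval in advance and repeat the between-group stool comparison without stools collected inside it. One month, matching the antibiotic look-back in section 2.2.1.3, would be a workable example; it is an assumption, not a known recovery time.
4. Keep all stools in the main analysis, and do not delay surgery to meet the interval.

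The cost is one date on a questionnaire that already asks about procedures, one added sentence in the protocol and one repeated comparison. The downside is fewer Group IV stools in the restricted comparison, and perhaps fewer in Groups II and III, with the loss of sensitivity shown in step 3. If almost no Group IV stools remain, only the interval by group can be reported, as a limitation of the stool results.

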#### Procedure

3.1.2

Highly experienced endoscopists, with proven adenoma detection rate of >30% will perform the colonoscopy, endoscopic polypectomy (if needed) and tissue sampling intended for the study. In case of CRC or endoscopically unresectable polyps, experienced abdominal surgeons specializing in colorectal surgery will take over the sampling procedure, as well. Patients will undergo simple polypectomy, endoscopic mucosal resection (EMR), endoscopic submucosal dissection (ESD), transanal endoscopic microsurgery (TEM) or surgery for CRC depending on the localization, size and histology of the lesion found. Procedures are scheduled as a common management of a colorectal neoplasm and will not be affected by patient’s preliminary enrolment in the study. During colonoscopy or colon resection the mucosal biopsy specimens from the polypoid lesion and the healthy gut (macroscopically healthy right- and left-sided colon and terminal ileum) will be obtained using disposable biopsy forceps (separate for each segment) to avoid bacterial contamination. The tissue sampling plan includes a) tissue of the terminal ileum; b) tissue of the right-sided colon (cecum, ascending colon, right colic flexure); c) tissue of the left-sided colon (descending colon, sigmoid colon and the rectosigmoid junction); and d) tissue of the lesion (if present). In case of small adenomas (<1 cm size), sampling is performed near the lesion, since multiple biopsies directly from the small tumor may result in artificial material fragmentation, at the same time raising the risk of histological misdiagnosis. Hyperplastic polyps and non-polypoid lesions are not being sampled, nor resected during colonoscopy in terms of the study. If multiple diverticula are present, normal tissue of the colon will be sampled at the least affected site. More than ten locoregional polyps are considered as polyposis and are not further investigated under this trial. Otherwise, while up to ten polyps are detected in the same colon region, the largest is being picked for sampling and subsequent investigation. Inflammatory or pseudo-polyps are not adenomatous lesions, thus are not considered eligible for the study. Bowel preparation should be evaluated with at least 6 out of 9 points according to the Boston Bowel Preparation Scale (BBPS), otherwise precise detection and evaluation of dysplastic mucosal lesions cannot be ensured. Those patients who underwent colonoscopy and have been evaluated by less than 6 points according to BBPS will not be included in further study. Resected or sampled polyps should be described using the Paris and NICE classifications. Each stool and tissue sample will be encoded according to localization of the colon and the type of examination it is dedicated for.

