##### Histopathological examination and further allocation

3.1.3.1

Biopsy specimens (resected polyps and samples of normal colonic and ileil mucosa) will be fixed in 10% buffer formalin 24-48 hours at room temperature, processed and embedded in paraffin (FFPE). The FFPE sample sections will be cut at 3 μm thickness and mounted on positively charged slides. All slides will be stained with hemotoxylin-eosyn (HE) for the accurate evaluation of polyps and healthy colon histology.

Patients with non-adenomatous mucosal and sessile serrated lesions will be eliminated from the study. Only patients with histopathologically confirmed colorectal adenoma (small/large), carcinoma *in situ* and adenocarcinoma are being selected for further examination and become study participants. These patients will be divided into 4 exposure groups according to the CR neoplasia size and the dysplasia level, and 4 self-control groups (patient serves as his own control), and the general control group V as an overall healthy patients’ control (**Table 2**). Patients with macroscopically normal but histologically confirmed adenomatous or non-adenomatous mucosal lesions in control-site biopsies will not be enrolled in further examination and so will be eliminated from the study.

**Table 2 T2:** Histology- and size-based allocation of participants.

Exposure	Control
Group I (N=10): endoscopically removed and histopathologically confirmed up to 1 cm sized (low-grade dysplasia) tubular/tubulovillous/villous adenoma;	Control group 1: biopsy samples from group I patients’ terminal ileum, right- and left-sided healthy colon;
Group II (N=10): endoscopically removed and histopathologically confirmed 1 cm or greater (low- or high-grade dysplasia) tubular/tubulovillous/villous adenoma;	Control group 2: biopsy samples from group II patients’ terminal ileum, right-and left-sided healthy colon;
Group III (N=10): endoscopically removed/sampled and histopathologically confirmed Ca *in situ* (high-grade dysplasia);	Control group 3: biopsy samples from group III patients’ terminal ileum, right- and left-sided healthy colon;
Group IV (N=10): endoscopically sampled and histopathologically confirmed invasive adenocarcinoma;	Control group 4: biopsy samples from group IV patients’ terminal ileum, right- and left-sided healthy colon;
Control group V (N=10): patients, without any polypoid lesions found during colonoscopy (mucosal biopsies from their terminal ileum, right- and left-sided healthy colon).	

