##### 16S rRNA gene sequencing for microbiota examination from tissue and fecal samples

3.1.3.3

Tissue samples including lesion (or para-lesion in case of small (<1cm) adenoma), right- and left-sided normal appearing colon and terminal ileum mucosa will be obtained from the participants during colonoscopy or surgery. Intestinal mucosal specimens will be frozen and stored in the − 80°C refrigerator for later use. Similarly, fecal samples of patients will be frozen and stored at − 80°C immediately after they have been received in the study centre.

The total DNA of frozen samples will be extracted by mechanical and enzymatical cell lysis. DNA integrity and concentration will be assessed by the NanoDrop ND-1000 spectrophotometer (Thermo, USA). The bacterial 16S rRNA V3–V4 regions will be amplified via polymerase chain reaction (PCR), and high-throughput sequencing will be conducted on an Illumina platform. Raw reads will undergo denoising and preprocessing utilizing the tools provided by the Quantitative Insights Into Microbial Ecology 2 (QIIME2) software pipeline platform using default settings, unless specified otherwise. The DADA2 workflow will be utilized to construct the amplicon sequence variants (ASV) table, and sequences will be aligned to build a phylogenetic tree. Low abundant sequences will be excluded from analysis. Taxonomic analysis will be conducted with a Naïve Bayes Classifier, leveraging on the SILVA 138.1 database.

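### In the 16S data, Group I lesions are represented by mucosa beside the adenoma and lesions of 1 cm or more by the lesion itself, so the Group I versus II contrast mixes stage with sampling position

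*Protocol article*

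**What the plan says.** **Sampling position.** Section 3.1.2 (Procedure) lists tissue of the lesion as the fourth sampling region, then makes an exception: "In case of small adenomas (<1 cm size), sampling is performed near the lesion". The reason given is that repeated biopsies of a small polyp could fragment it and endanger the histological diagnosis. Section 3.1.3.3 carries the exception into the sequencing material: "Tissue samples including lesion (or para-lesion in case of small (<1cm) adenoma), right- and left-sided normal appearing colon and terminal ileum mucosa".

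**Group boundary.** Table 2 defines Group I as low-grade adenomas up to 1 cm and Group II as adenomas of 1 cm or more. Groups III and IV (carcinoma in situ and invasive cancer) have no size limit.

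**What is compared.** Section 3.1 makes differences in microbiota and immune infiltration across the dysplastic steps, against healthy controls, the primary outcome. One task in section 1.2 is to determine the microbiota of the early adenoma itself. Section 5.1 predicts larger changes in polyps of 1 cm or more than in smaller ones.

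**Resected polyps.** Section 3 (Interventions) says: "Resected polyps and mucosal biopsy specimens from unaffected bowel regions will be sent to histological, IHC, DNA sequencing examination". It makes no exception for small adenomas. Section 3.1.3.1 also describes the paraffin-embedded material as resected polyps plus normal mucosa.

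**Group IV route.** Table 2 describes these patients as "endoscopically sampled and histopathologically confirmed invasive adenocarcinoma". Section 3.1.2 says that for colorectal cancer, or polyps that cannot be removed endoscopically, "experienced abdominal surgeons specializing in colorectal surgery will take over the sampling procedure". Table 1 lists "normal gut tissue sampling or right hemicolectomy and gut tissue sampling" as part of one sampling event.

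**The concern.** The size that decides where the biopsy is taken is the same size that decides the group. Under these rules Group I contributes adjacent mucosa to the lesion-level 16S comparison, and Group II contributes dysplastic tissue. If the two tissues carry different bacterial communities, a step from early to advanced adenoma will appear even where stage has no effect.

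Section 5.1 itself treats the two tissues as informative about different things: neoplastic tissue about passenger bacteria, non-neoplastic tissue of the same gut about driver bacteria. If adjacent mucosa lies closer to normal than the lesion does, the bias also runs in the direction that section 5.1 predicts for size.

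Biopsies are taken once and no further study visits are planned, so the problem cannot be repaired later. The limitations section does not mention it.

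**Working it through.** **1. The plan's own counts.** Four exposure groups of 10 with four regions, and 10 controls with three regions, give 40 × 4 + 10 × 3 = 190 locations. Then 190 × 3 = 570 tissue samples and 570 × 4 = 2280 stained specimens. All three agree with section 2.2.4. They also show two things:
- The Group I para-lesional site is counted as that patient's lesion location.
- The 570 sequenced tissue samples amount to 570 / 190 = 3 per location. With 3 more for histology, 6 of the 7 biopsies per region are used.

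The figure of 10 per group cannot be reproduced, because no endpoint, effect size or SD is given. The point does not depend on it.

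**2. Can position be separated from stage?** Let G2, G3 and G4 indicate Groups II to IV, and let P = 1 for a para-lesional sample. If only Group I is sampled beside the lesion, P = 1 − G2 − G3 − G4. The design matrix (intercept, G2, G3, G4) has rank 4, and adding P leaves it at 4. For Groups I and II:

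observed difference = stage difference + position difference

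This is one equation with two unknowns. Redundancy analysis could list position as a factor but meets the same identity. ANOSIM, ANCOM, LEfSe and Kruskal-Wallis with Dunn's test compare the groups as sampled.

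**3. How far it extends.** For I versus II the overlap follows directly from the 1 cm rule. For I versus III or IV it is large but not assured: Group III has no size limit, so a carcinoma in situ under 1 cm might also be sampled beside the lesion. Biopsies of ileum, right colon and left colon, and stool, follow one rule in all groups and do not depend on lesion position.

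**4. Illustration of size.** The documents give no difference between adjacent and lesional tissue, so the offsets are assumptions. Simulation: normal data, SD 1, 10 per group, no stage effect, offset applied to Group I only, two-sided 0.05, 4000 runs per offset.

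| Assumed offset (SD) | I vs II, Mann-Whitney | I–IV, Kruskal-Wallis |
|---|---|---|
| 0 | 4% | 4% |
| 0.25 | 7% | 7% |
| 0.5 | 16% | 15% |
| 1.0 | 52% | 53% |

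The simulation standard error is at most √(0.5 × 0.5 / 4000) = 0.8 percentage points. The table describes a single continuous measure such as a diversity index. It does not describe ANOSIM or taxon-level tests.

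**5. Immune data, side by side.** Section 3.1.2 takes the study biopsies beside small lesions. Sections 3 and 3.1.3.1 process the resected polyp for histology and immunohistochemistry. Group I immune measurements could therefore come from either tissue. Section 3 also sends resected polyps to sequencing, which does not fit 3.1.3.3.

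**The case against.** The para-lesional rule is deliberate, disclosed twice and has a practical reason. Parts of the article speak of patterns around the lesion, which adjacent mucosa fits. The primary outcome is worded against healthy controls, and the size comparison appears as an expectation rather than a named test. Each exposure group also has its own normal mucosa as control.

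Some of this stands. The rule may well be right for a small polyp, and Group I against its own normal mucosa or against healthy controls can be interpreted as a para-lesional comparison. It does not rescue the cross-stage contrast. Larger lesions are not sampled around but within, the dysplastic steps belong to the primary outcome, and self-controls are normal mucosa in every group, so they do not remove the difference in position.

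A reader might infer more than the documents support:
- **That the immune data are equally confounded.** They are ambiguous, because resected polyps go to immunohistochemistry.
- **That Group IV is confounded with surgery.** Table 2's wording may describe how the diagnosis was made, and surgeons may also sample unresectable polyps, so the route is not unique to Group IV.
- **That the 190 sites are unattainable because a right hemicolectomy specimen lacks left colon.** Nothing says that all four regions come from the resection specimen. Tumours that prevent complete colonoscopy are excluded, so left-colon biopsies can be endoscopic.

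**Conclusion.** The point holds for the lesion-region 16S samples. Group I versus II is fully aliased with adjacent versus dysplastic tissue, and Group I versus III or IV largely so. This follows from the sampling rule and Table 2 alone and needs no assumed effect size. How often it would mislead does depend on assumption: about 7% to 52% false significance for offsets of 0.25 to 1.0 SD, against about 4% with none.

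For the immune data, the finding is that sections 3, 3.1.2, 3.1.3.1 and 3.1.3.3 must be reconciled on which tissue is stained and which is sequenced. For Group IV, it is that Table 1, Table 2 and 3.1.2 must be reconciled on route.

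**What to change.** 1. **Immune data.** State that the Group I lesion specimen for immunohistochemistry and image analysis is the paraffin section of the resected polyp. Align sections 3, 3.1.2, 3.1.3.1 and 3.1.3.3 accordingly, including whether resected polyps are sequenced.
2. **16S data.** Within the seven lesion-region biopsies already planned, take some of the Group II to IV sequencing biopsies from adjacent mucosa. Base every cross-stage 16S contrast involving Group I on the para-lesional samples that all groups then share. In-lesion samples remain available for contrasts among Groups II to IV.
3. **If sampling is already complete.** Compare the Group I para-lesional sample only with the same patients' normal mucosa and with healthy controls. State that lesion-level 16S differences between Group I and later groups will not be read as stage effects.
4. **Position and route.** Record both for every specimen, reconcile the three places on Group IV, and add a sensitivity analysis by route. Restricting Group IV to endoscopic samples is not advised, since it could leave few of the 10 patients.

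Cost: a change to the sampling instructions and some analysis wording, with no extra biopsies. The price is fewer in-lesion 16S biopsies per patient in Groups II to IV, where the counts imply three per location. The fallback in item 3 costs only wording, but gives up the lesion-level 16S reading of the first step in the sequence.
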